## Abstract

Early-onset colorectal cancer (EOCRC) is defined as a diagnosis of colorectal cancer (CRC) in individuals younger than 50 years of age. While overall CRC rates in the United States (US) decreased between 2001 and 2018, EOCRC rates have increased. This research project aims to evaluate the feasibility and acceptability of Time-Restricted Eating (TRE), Mindfulness, or TRE combined with Mindfulness among young to middle-aged adults at risk of EOCRC. Forty-eight participants will be randomly assigned to one of four groups: TRE, Mindfulness, TRE and Mindfulness, or Control. Data on feasibility, adherence, and acceptability will be collected. Measures assessed at baseline and post-intervention will include body weight, body composition, dietary intake, physical activity, sleep behavior, circulating biomarkers, hair cortisol, and the gut microbiome. The effects of the intervention on the following will be examined: (1) acceptability and feasibility; (2) body weight, body composition, and adherence to TRE; (3) circulating metabolic, inflammation, and oxidative stress biomarkers; (4) intestinal inflammation; and (5) the gut microbiome. TRE, combined with Mindfulness, holds promise for stress reduction and weight management among individuals at risk of EOCRC. The results of this pilot study will inform the design and development of larger trials aimed at preventing risk factors associated with EOCRC.

## 1. Introduction

Early-onset colorectal cancer (EOCRC) is defined as a diagnosis of colorectal cancer (CRC) in individuals younger than 50 years of age. While overall CRC rates in the United States (US) decreased between 2001 and 2018, EOCRC rates increased in non-Hispanic White, Hispanic, American Indian, and Alaska Native adults but remained stable in adults identifying as non-Hispanic Black and Asian and Pacific Islander [1,2]. EOCRC is increasing more rapidly in Westernized countries, which suggests that exposure to similar risk factors common to Western culture is a contributor to EOCRC development. Approximately only 20% of new cases are attributed to genetic causes [3], which suggests that the majority of cases are attributed to modifiable risk factors rather than hereditability.

EOCRC shares many risk factors with CRC, including excess adiposity, diet quality, and microbiome dysregulation [4,5]. Obesity early in adulthood that persists with aging is strongly associated with an increased risk of EOCRC [6]. This is a concern since obesity affects 40% of young adults (20–39 years of age) in the US [7]. Obesity is associated with metabolic, hormonal, immune (i.e., insulin resistance, increased systemic inflammation, and oxidative stress), and gut microbial perturbations that can promote gene mutations that drive EOCRC tumorigenesis [8]. This suggests the importance of weight management as a preventive approach to EOCRC.

Stress may also increase the risk of EOCRC. The prevalence of perceived psychosocial stress in young adults varies widely, with studies reporting rates ranging from 20% [9]–60% [10]. Chronic psychosocial stress (CPS) adversely affects several systems of the human body, with implications for tumorigenesis. CPS can over activate the hypothalamic–pituitary–adrenal axis and sympathetic nervous system, augmenting the release of hypothalamic-pituitary-adrenal mediators such as adrenocorticotropic hormone and cortisol and sympathetic nervous system mediators such as epinephrine and norepinephrine. Cortisol can adversely impact cell cycle control and reduce DNA repair to promote carcinogenesis [11]. In response to stress, norepinephrine and epinephrine potentiate their effects on adrenergic receptors. Chronic activation of β-adrenergic receptors specifically has been implicated in carcinogenesis, with their activation affecting inflammation, proliferative signaling, genome instability, and immune evasion, which are well-established “hallmarks of cancer” [11,12,13,14]. Furthermore, studies have shown the negative effects of CPS on eating behavior (increased appetite and preference for energy-dense foods) [15], decreased insulin sensitivity [16], increased overall and central adiposity [17], increased systemic inflammation [18], and gut microbiome dysbiosis [19], resulting in an inflamed gut [20,21]—all known risk factors for colorectal carcinogenesis [22]. This suggests the importance of addressing CPS as a modifiable risk factor for the EOCRC. 

Time-Restricted Eating (TRE) may be a salient and effective approach to weight management and EOCRC prevention among individuals with obesity and CPS. TRE is a popular type of intermittent fasting that produces a ~300–500 kcal daily energy deficit by simply limiting an individual’s eating window to 4–8 h each day [23]. Individuals following TRE are asked to limit food intake to a specified time frame (e.g., 12 p.m.–8 p.m.) and no-calorie fast (i.e., only consume water or zero-calorie beverages) for the remaining hours of the day. Studies of TRE in humans show high adherence among both younger and older adults with obesity and clinically meaningful weight loss (over >5% weight loss). Moreover, TRE is associated with improvements in insulin sensitivity, systemic inflammation, oxidative stress, circulating insulin-like growth factor 1, and leptin, indicating its potential applicability for preventing EOCRC [24,25,26]. Given its simplicity, TRE may also be more acceptable for weight management among individuals with CPS compared to traditional calorie restriction given that TRE does not require individuals to count calories and continuously monitor their intake, which may serve as an additional stressor. 

Mindfulness could also play a role in cancer risk reduction. Mindfulness meditation is the practice of cultivating a moment-to-moment awareness of internal and external experience in an accepting and open manner that includes the tenets of Kabat-Zinn’s Mindfulness-Based Stress Reduction [27]. Attitudes of open inquiry, patience, suspended judgment, and compassion are encouraged and cultivated during intervention sessions. Individuals are taught to focus attention on sensations of breath, body, and objects that enter awareness, such as thoughts and emotions, with the intention to fully experience the present moment. Protocols with different forms of intervention delivery (e.g., online vs. in-person) or with protocol changes (e.g., removal of Hatha yoga) are being tested to evaluate their efficacy for reducing CPS. Mindfulness interventions have demonstrated positive effects on perceived stress [28] and on circulating cortisol concentrations [19,29]. Existing evidence also suggests that Mindfulness yields EOCRC preventive effects specific to body weight [30], insulin sensitivity [31], and systemic inflammation [32]. Small studies have tested the effects of Mindfulness on cardiovascular disease risk [33], glycemic control [34], stress reduction [35], and chronic pain management [36] with positive outcomes. However, studies have yet to prospectively investigate the effect of Mindfulness on cancer risk reduction. 

It is possible that Mindfulness interventions could reduce cancer risk in an at-risk population through multiple pathways, including physiological stress regulation, eating behavior, and immune regulation. The release of glucocorticoids (cortisol in humans and corticosterone in animals) is dysregulated in the presence of CPS. With CPS, there is a high influx of glucocorticoids, which results in prolonged activation of the hypothalamic–pituitary–adrenal axis, which may affect two established hallmarks of cancer: genome instability and tumor-promoting inflammation [11]. One meta-analysis assessed 45 articles and found a medium effect of meditation (a component of Mindfulness) in reducing circulating cortisol (through multiple different types of cortisol assessment: salivary, hair, and blood). Meditation applies to the Mindfulness scope as it is part of the standard protocol [37]. By reducing cortisol levels, Mindfulness practices likely diminish inflammation and genome instability, leading to cell mutations. 

Obesity is a modifiable risk factor for several cancers, including colorectal cancer [38]. Several studies have evaluated the effects of Mindfulness on eating behavior to support weight management. Stress-induced emotional eating is often associated with the consumption of “comfort foods” that tend to be more energy dense [39]. To determine the effect of Mindfulness on eating behavior, Fulwiler et al. used the “Three-Factor Eating Questionnaire”, an assessment that measures three aspects of eating behavior: cognitive restraint, uncontrolled eating, and emotional eating, to determine if emotional eating shifted in response to a Mindfulness intervention [40]. They presented the hypothesis that high levels of emotional eating could predict weight gain, while low levels of emotional eating could predict weight loss. They found in their study that Mindfulness was associated with reduced levels of emotional eating, but they failed to assess participant weight change [40]. A systematic review and meta-analysis conducted in 2019 evaluated 10 Mindfulness interventions on weight control and found a significant weight reduction among the Mindfulness participants when compared to control groups [41]. Therefore, Mindfulness may reduce emotional eating, energy intake, and weight gain, thus reducing the risk of colorectal cancer.

This paper describes the design of a TRE and Mindfulness intervention among young adults with obesity and CPS. Participants will be randomized to 8 weeks of TRE, Mindfulness, TRE and Mindfulness, or Control. The primary outcomes are related to feasibility and acceptability. Secondary outcomes are related to body weight, body composition, perceived stress, metabolites of the hypothalamic–pituitary–adrenal axis, circulating cardiometabolic disease risk markers, gut microbiome, and colonic inflammation. We hypothesize that the study will be feasible (i.e., recruit ≥ 50% of those approached, retain ≥ 80% of the participants, participants in the intervention groups will complete ≥ 80% of the intervention content, and all groups will complete ≥ 80% of planned assessments) and acceptable (i.e., based on a standardized acceptability survey by Pflugeisen et al. [42], that will be assessed during week 4 of the intervention and after completing the intervention). 

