#### 2.4.1. Time-Restricted Eating (TRE)

Participants will be instructed to eat ad libitum from 12:00–8:00 p.m. daily and fast during the remaining hours (16-h fast). The set eating window was selected based on an observational study of 800,000 North Americans, which found that individuals usually place their TRE eating window from 12–8 p.m. so that they can have lunch and still eat dinner with friends and family [44]. During the 8-h eating window, there will be no restrictions on the types or quantities of foods consumed. In addition, participants will not be required to monitor calorie intake. During the fasting period, participants will be encouraged to drink plenty of water and consume energy-free beverages only, such as black tea or coffee. Participants will meet with a registered dietitian for 30 min at the start of the intervention to review instructions and goals and weekly thereafter. Weeks 2–8 will focus on TRE adherence and personalized problem solving related to adherence to the TRE intervention. Each day, participants will respond to a text message to indicate their eating start and stop times. If the message indicates that the participant ate only within the prescribed eating window (±30 min of 12 p.m. and + 30 min of 8 p.m.), that day will be labeled “adherent”, otherwise the day will be labeled “non-adherent.” On the same day and time each week, participants will be asked to transmit a picture of their weight from a home scale via a secure text-messaging platform. Participants will be asked to maintain their baseline level of physical activity.

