### 2.7. Data Analytic Plan

Data will be managed using REDCap [72] and analyzed using the statistical software SAS (version 9.4, SAS Institute, Cary, NC, USA). The data will be organized and stored on an encrypted server. Metadata will be available and stored in an electronic lab notebook, including details of what, where, when, why, and how data were collected and processed. 

We will summarize feasibility and acceptability metrics using descriptive statistics such as frequencies, percentages, means, and standard deviations. The results will include the recruitment rate among eligible individuals approached, adherence (i.e., % interaction with asynchronous sessions, % of days adherent to the TRE protocol), % retained through post-intervention, and scores on the acceptability survey. The feasibility and acceptability rates will be estimated as the number of feasibility and acceptability participants divided by the total number of approached participants, respectively. A 95% confidence interval for the feasibility and acceptability rates will be calculated assuming a binomial distribution. Fisher’s exact test will be used to test whether feasibility and acceptability rates are significantly higher than their threshold rates (50% or 80%), respectively. A chi-square test will be used to test its relationship with other categorical clinical factors, and a *t*-test will be used for its relationship with other continuous clinical factors instead. Adjusted logistic regression (binary outcomes) or generalized linear models (GLM) (continuous outcomes) will be employed in multivariate analyses to assess their relationship with each other as clinical factors. 

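### No feasibility threshold is clearly tied to eating-window adherence, because 'intervention content' is undefined for the TRE arms

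*Protocol article*

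**What the plan says.** The Introduction of the protocol article names feasibility as a primary outcome and defines it by a closed list of four criteria. Three concern recruitment (at least half of the people contacted), retention (at least 80%) and completion of assessments (at least 80%, in every arm). The fourth, on delivery, is that "participants in the intervention groups will complete ≥ 80% of the intervention content".

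Section 2.7 lists what will be reported, including "adherence (i.e., % interaction with asynchronous sessions, % of days adherent to the TRE protocol". It then plans tests of feasibility and acceptability rates against 50% or 80%, without saying which metric takes which threshold. The rates themselves are "estimated as the number of feasibility and acceptability participants divided by the total number of approached participants".

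Section 2.4.1 describes TRE delivery: "Participants will meet with a registered dietitian for 30 min at the start of the intervention to review instructions and goals and weekly thereafter". Section 2.4 says that intervention sessions run by videoconference. Section 2.4.1 also classifies every day as adherent or not from a daily text message. Section 2.4.2 sets 30 audio lessons for Mindfulness, and section 2.4.3 gives the combined arm both protocols. Section 2.8.4, however, describes the Mindfulness and TRE intervention as asynchronous.

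**The concern.** Keeping to the eating window is the behaviour that makes up TRE, and section 2.8.3 itself expects it to be challenging. Yet none of the four criteria names it. The only criterion that could cover it uses a word, content, that the article does not define for TRE. The one session metric in section 2.7 does not fit the live dietitian meetings, and attendance at those meetings is not a listed metric.

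The trial exists to inform a larger one (section 2.6.12). If the success criterion can be read in two ways, the reading can be chosen after the adherence data are seen. A TRE arm could then be called feasible on session attendance although its participants seldom kept to the window.

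**Working it through.** The plan gives no figure for this criterion beyond the 80%. Its one power statement (section 2.6.12) concerns continuous outcomes and plays no part here.

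**Inputs**
- Lessons: 4 × 7 + 2 = 30 (section 2.4.2), which agrees with Table 2.
- Dietitian meetings: one at the start and then weekly, taken as 8 (assumption: one per week for 8 weeks).
- Days: 8 × 7 = 56, if no day is excused.
- Participants: 48 randomised 1:1:1:1, so 12 per arm and 24 in the two TRE arms (section 2.3.4).

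**Reading A: content means session material.** Required count = 80% of items, rounded up.
- TRE: 0.8 × 8 = 6.4, so 7 of 8 meetings.
- Mindfulness: 0.8 × 30 = 24 of 30 lessons.
- Combined arm, items pooled: 0.8 × 38 = 30.4, so 31 of 38.

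None of these needs an adherent day. Recruitment, retention and assessment completion do not need one either. On this reading all four criteria can be met with 0 of 56 adherent days.

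**Reading B: content covers the adherence metrics of section 2.7.** The TRE mark is 0.8 × 56 = 44.8, so 45 of 56 adherent days, and the problem disappears.

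**Which reading does the text favour?**
- For A: section 2.5 uses content for what is covered in sessions, the title of Table 2 uses it for the lessons, and the abstract lists adherence to TRE under a different aim from acceptability and feasibility.
- For B: section 2.7 puts adherent days among the feasibility and acceptability results and then mentions an 80% threshold.
- Neither is decisive.

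**Can a threshold on adherent days be tested?** Suppose each participant either meets the 45-day mark or does not, and the arm's proportion is tested against 80%, one-sided at 0.05 (assumption).
- One arm, 12 of 12: p = 0.8^12 = 0.069. The best possible result is not significant.
- Both TRE arms, 23 of 24: p = 24 × 0.8^23 × 0.2 + 0.8^24 = 0.028 + 0.005 = 0.033. Nothing less than 23 of 24 reaches 0.05.
- Described only, the smallest counts at or above 80% are 10 of 12 (exact 95% CI 52% to 98%) and 20 of 24 (63% to 95%).

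**The case against.** The strongest reply is that TRE adherence is not neglected. It is defined day by day, collected by text, supported in weeks 2 to 8 and reported with the other feasibility results, where an 80% threshold is also mentioned. Poor adherence would be visible beside any statement of feasibility, and the article gives no go/no-go rule that depends on the four criteria. An article may also leave the definition of content to the full protocol.

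Much of this stands, and it rules out three stronger inferences that a reader might draw:
- That nothing in the plan requires fasting. This takes Reading A as settled, and the documents leave Reading B open.
- That the combined arm can pass on audio lessons alone. Section 2.4.3 assigns it both protocols. On a pooled count 24 lessons are 24/38 = 63%, and all 30 are 30/38 = 79%, both below 80%.
- That the TRE arm certainly has no asynchronous sessions. Section 2.8.4 says otherwise, so this is a contradiction to reconcile and not an established fact.

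The appeal to condensation does not remove the point. The article itself sets out the success criteria of a primary outcome as a closed list, and those criteria admit both 0 of 56 and 45 of 56 adherent days. Reporting adherence makes a poor result visible but does not fix beforehand what counts as success.

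**Conclusion.** The concern holds in a limited form. Eating-window adherence is measured and reported, but no success threshold is clearly tied to it. Content is undefined for TRE, and the listed session metric does not match the sessions described in sections 2.4 and 2.4.1. On the session reading, TRE could be declared feasible despite poor window adherence. On the other reading, 80% of days is already required. The text does not settle which applies.

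The ambiguity spans 0 to 45 of 56 days per participant and affects two of the three intervention arms, 24 of 48 participants. These counts assume one dietitian meeting a week and no excused days. The criterion should be fixed before adherence data are examined. It is a weakness in how feasibility is defined and not evidence that the plan overlooks adherence.

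**What to change.** In the Introduction and section 2.7, apply the existing 80% by component:
- **Mindfulness:** at least 24 of 30 lessons completed.
- **TRE:** at least 80% of scheduled dietitian sessions attended (7 of 8 if there are eight) and, as a separate mark, at least 80% of scheduled days adherent. That is 45 of 56 with no excused days. Section 2.8.1 allows an off day on major holidays, so one such day would give 0.8 × 55 = 44.
- **Combined arm:** assessed on both components.

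Use everyone randomised to the arm as the denominator. The approached total in section 2.7 includes people who were never assigned an intervention. Count an unanswered daily text as not adherent, with a sensitivity analysis on answered days only. Report the proportion of participants meeting each mark, by arm, with an exact confidence interval and no test against 80%.

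Reconcile the description of sessions as asynchronous in sections 2.7 and 2.8.4 with the meetings in sections 2.4 and 2.4.1, and list dietitian-session attendance as a metric.

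The daily texts and weekly meetings are already planned, so the added work is to log attendance and revise the text. The real cost is that these are firmer success criteria, and the feasibility claim for the two TRE arms becomes harder to meet.

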## 2. Materials and Methods

The experimental protocol was approved by the University of Illinois, Chicago (IRB# 2020-0498) on 18 August 2023. Participants will provide written informed consent prior to study participation. The trial is registered at ClinicalTrials.gov (NCT06022887) since 1 September 2023.

### 2.1. Study Design 

This study is an 8-week, parallel-arm, randomized controlled trial (Figure 1). A total of 48 young adults (18–39 years old) with obesity [body mass index (BMI) between 30–49.9 kg/m^2^] and a Perceived Stress Score ≥ 14 [43] will be randomized 1:1:1:1 to the following groups: 1. TRE; 2. Mindfulness; 3. TRE and Mindfulness; or 4. Control.

### 2.2. Setting and Recruitment

A total of 48 individuals residing in the Chicago land area will be recruited and enrolled. Recruitment will take place through social media, listserv emails, postcards, and Researchmatch.org. Interested participants will complete an online survey using a link shared through the recruitment materials. If they are found to be eligible based on the survey answers, they will be contacted via phone call and invited to come for an in-person screening. Data collection visits will take place at the University of Illinois Chicago. 

### 2.3. Participants

#### 2.3.1. Screening

Individuals interested in participating will first complete a survey to assess eligibility using a link shared via email. If an individual meets the basic inclusion criteria, they will be invited to an in-person screening to complete informed consent. They will be asked to fast for 12 h prior to their in-person screening. Individuals will be weighed using an electronic scale, and height will be assessed with a fixed stadiometer to confirm BMI (kilograms per meters squared). Individuals meeting all screening metrics (Table 1) will be invited to participate in the full trial. If the participant is eligible based on their height and weight, arrived after fasting for 12 h, and is interested in continuing in the study, baseline data collection will immediately commence. 

#### 2.3.2. Inclusion Criteria

The inclusion criteria are as follows: 18 to 39 years of age, a BMI of 30–49.99 kg/m^2^, ≥14 on the Perceived Stress Survey (PSS) [43], and owning and using a smartphone, computer, or tablet with access to the Internet.

#### 2.3.3. Exclusion Criteria

Exclusion criteria for the study includes: personal or family history of EOCRC; oral or intravenous antibiotics in the past two months; inflammatory bowel disease; genetic predisposition to colorectal cancer (e.g., Lynch syndrome); a cancer diagnosis or cancer treatment in the past 12 months; consumption of more than 50 g of ethanol daily (approximately equivalent to 4–5 12-ounce beers); combustible tobacco use; history of bariatric surgery or bowel resection; active infection; type 1 or type 2 diabetes; immunodeficiency/autoimmune disorders; using fiber or pre-/probiotic supplements > three days per week; taking corticosteroid medication (inhaled, topical, or oral) within the past two months; participating in a formal weight-loss program or those who have not maintained weight stability for three months with fluctuations—4.5 kg prior to the study; females who are pregnant or trying to become pregnant; individuals with active diagnose of any mood or eating disorders; currently following an intermittent fasting pattern or an eating window ≤ 10 h; night shift workers (shift that extends past midnight); history of eating disorder; currently taking weight loss medication; and self-reported use of illegal drugs in the past month (excluding marijuana).

